**Methods/design:**

Adults with moderate to severe stroke impairment (National Institutes of Health Stroke Scale (NIHSS) score 5 to 25 at the time of admission) are recruited within 2 weeks of stroke onset. Participants must be able to perform voluntary respiratory maneuvers. Excluded are patients with increased intracranial pressure, uncontrolled hypertension, neuromuscular conditions other than stroke, medical history of asthma or chronic obstructive pulmonary disease, and recent cardiac events. Participants are randomized to receive inspiratory, expiratory, or sham respiratory training over a 4-week period, by using commercially available threshold resistance devices. Participants and caregivers, but not study investigators, are blind to treatment allocation. All participants receive medical care and stroke rehabilitation according to the usual standard of care. The following assessments are conducted at baseline, 4 weeks, and 12 weeks: Voluntary and reflex cough flow measurements, forced spirometry, respiratory muscle strength tests, incidence of pneumonia, assessments of safety parameters, and self-reported activity of daily living. The primary outcome is peak expiratory cough flow of voluntary cough, a parameter indicating the effectiveness of cough. Secondary outcomes are incidence of pneumonia, peak expiratory cough flow of reflex cough, and maximum inspiratory and expiratory mouth pressures.

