## Methods/design

### Study design

The study is a pilot study, designed as a single-blind randomized controlled trial with three study groups. Participants are randomized to receive inspiratory muscle training, expiratory muscle training, or sham RMT. After the baseline assessment, participants undergo a 4-week intervention period. Weekly investigator visits are conducted during the intervention period. The primary study end point is at the end of the intervention period (day 29). A final reassessment is conducted at 12 weeks after baseline. One investigator conducts all study procedures, including screening for eligibility, gaining consent, conducting study assessments, and introducing and assisting with the intervention. A summary of the study timeline and all data collected is given in Additional file
1. The participant flow through the study is described in Figure 
1.

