### Randomization, blinding, and treatment allocation

Sequentially numbered sealed envelopes containing the treatment allocation were prepared by a researcher unrelated to the study team. The randomization sequence was computer-generated. Block randomization (blocks of 12, containing four participants per study arm) was used to ensure even participant spread across the trial groups.

For each participant, the investigator opens the respective envelope after informed consent has been gained and immediately before conducting the study baseline session. Thereafter, the investigator is aware of the participant’s group allocation. Participants, caregivers, and healthcare professionals are unaware of group allocation throughout the study period.

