For the off-site system, a different analog-to-digital converter (NI BNC-2110; National Instruments, Newbury, England) and laptop with data-acquisition software (LabView, version 5.1, National Instruments) are used. The on-site and off-site systems have the same performance characteristics: linear response from zero to 700 L/min in both directions of flow; frequency response of >20 Hz; and analog-to-digital sampling of 2 kHz. The systems are calibrated before each testing session by two-point calibration with a rotameter (InFlux OF1”S, 60 to 600 L/min flow; Techniquip Ltd, Taunton, England) at a reference flow of 500 L/min.

Voluntary and reflex coughs are assessed. For voluntary coughs, participants make repeated maximal cough efforts into a tight-fitting face mask, until five coughs of similar PECF are recorded. To elicit reflex coughs, escalating concentrations of capsaicin (0.49 to 1,000 μ*M*) are nebulized (UltraNeb U3000; DeVilbiss Healthcare Ltd, Tipton, England) and introduced into the face mask for 1 minute at a time, until the threshold is reached at which five bouts of reflex coughing are triggered. From the recorded cough-flow traces, the following parameters are derived for the five voluntary and five reflex coughs with the highest peak expiratory flow rates: peak expiratory cough flow (PECF), peak inspiratory cough flow (PICF), volume expired (VE), volume inspired (VI), glottis compression time, and cough-volume acceleration.

To monitor the safety of the intervention, blood pressure, heart rate, and blood oxygen saturation are measured before and after participants carry out RMT. Measurements are made by using a digital blood pressure monitor (UA-767 Plus; A&D Instruments Ltd, Abingdon, Oxon, UK) and a finger pulse oximeter (Onyx 9500; Nonin Medical Inc, Plymouth, MN, USA). In addition, the investigator notes any subjective discomfort reported during training. Adverse events are noted and reviewed throughout the duration of the study.

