### Weaknesses

The methods for identifying the presence of swallowing difficulty and pneumonia in the current study may be regarded as a limitation. To minimize participant burden created by additional medical procedures, it was decided to take a pragmatic approach and observe clinical and self-reported information on swallowing function and pneumonia. A more-detailed instrumental assessment of swallowing, such as video-fluoroscopic examination of swallow, could be used to determine the degree of dysphagia and aspiration. Objective diagnostic criteria for pneumonia, including assessments of chest radiographs and blood results
[69,70], could be used to support the detection of pneumonia.

A further limitation to the study is the lack of investigator blinding. The investigator is masked to treatment-allocation sequence, but is aware of group allocation from the point of randomization.

Although the clinical purpose of this research is to reduce the risk of pneumonia after stroke, the study uses voluntary cough flow as a surrogate primary outcome. This surrogate outcome was selected to minimize the required sample size. Designing the study according to the primary outcome, pneumonia, would require a considerably larger sample. For example, it could be assumed that both intervention groups would show a reduction in pneumonia rates from 15% to 7.5% compared with the control group. To give 80% power at the 5% significance level, this would require approximately 180 participants per group (using the χ^2^ test and not accounting for attrition).

The choice of voluntary cough flow as a surrogate primary outcome in this study was based on the physiological rationale to the research. Also, good evidence shows that reduced voluntary cough flow in stroke patients is associated with higher risk of aspiration, and therefore aspiration pneumonia
[35,36]. To our knowledge, the direct relation between voluntary cough flow and pneumonia has not been investigated in stroke populations. The importance of cough flow may be inferred from populations with neuromuscular conditions, where reduced levels of voluntary cough flow indicate the need for assisted airway clearance

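### Deriving cough flow from the stored traces could be masked without another assessor, but the article describes no masking at this step

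*Protocol article*

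**What the plan says.** Under Study parameters, cough flow passes through an analog-to-digital converter to a laptop, with one system on site and another off site. The derivation is described thus: "From the recorded cough-flow traces, the following parameters are derived" "for the five voluntary and five reflex coughs with the highest peak expiratory flow rates". The first derived parameter listed is PECF. Voluntary-cough PECF at day 29 is the primary outcome, and reflex PECF is a secondary outcome.

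On who does the work, Study design states: "One investigator conducts all study procedures, including screening for eligibility, gaining consent, conducting study assessments, and introducing and assisting with the intervention". The randomization section has this investigator open the envelope just before the baseline session, and adds: "Thereafter, the investigator is aware of the participant’s group allocation". The abstract agrees: "Participants and caregivers, but not study investigators, are blind to treatment allocation".

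The Weaknesses section acknowledges the consequence in general terms: "A further limitation to the study is the lack of investigator blinding". It sets out no measure to reduce the effect on the reading of the traces.

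**The concern.** Producing a PECF value involves two separable steps. Acquisition takes place with the participant: fitting the mask, coaching maximal efforts, deciding when enough coughs have been recorded. A lone investigator who also sets the training resistance cannot be masked for this. Derivation takes place on a stored file, and nothing in it requires knowledge of the arm or the visit.

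The article treats lack of blinding as one undivided limitation and leaves the second step apparently unmasked. If a doubtful peak is accepted more readily in one arm than in another, the result is a directional error in the primary outcome and in reflex PECF. The planned ANCOVA and imputation approaches would not detect or remove it. The Statistical analysis section also says that the analysis plan was revised as data accumulated. Outcome values fixed before linkage to allocation would therefore add credibility at little expense.

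**Working it through.** **Who reads the traces, and with what knowledge**

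1. Stored traces exist: Study parameters describes digital recording on both systems.
2. PECF is derived from those recordings (same section). The sentence is passive and names no reader.
3. One person does all study procedures (Study design). The examples listed are participant-facing, and trace processing is not among them. That the same person reads the traces is a strong inference, not a stated fact.
4. That person knows the arm before any trace is recorded, baseline included (Randomization, blinding, and treatment allocation).
5. No coding of files, masked reading or automated extraction is described, and no rule says which deflections count as a valid cough.

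**How large could it be?**

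The article gives no figure for reading error and no within-person spread of cough efforts, so there is no plan figure to reproduce. What follows is illustration only.

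Assumptions, none of them in the article: 8 normally distributed efforts per session, a within-person SD of 15, 30 or 45 L/min, rejection of the top peak as artefact, and this happening in a quarter more participants in one arm than in another.

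The expected normal order statistics for 8 efforts, in SD units from the top, are 1.424, 0.852, 0.473, 0.153, −0.153, −0.473 and so on. The article does not say how the five values are summarised, so two cases are shown.

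- Mean of the five highest: losing the top value and gaining the sixth lowers it by (1.424 + 0.473)/5 = 0.379 SD, which is 5.7, 11.4 or 17.1 L/min in an affected participant. A quarter of this is 1.4 to 4.3 L/min between arms.
- Single highest cough: the fall is 1.424 − 0.852 = 0.571 SD (from unrounded values), or 8.6 to 25.7 L/min. A quarter is 2.1 to 6.4 L/min between arms.

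**Against the noise in the trial**

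The Sample size section reports group SDs of about 100 to 250 L/min and plans 20 completers per group. The standard error of a pairwise difference is SD × √(2/20):

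- SD 100: 100 × 0.316 = 31.6 L/min
- SD 250: 250 × 0.316 = 79.1 L/min

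The illustrative shift of 1.4 to 6.4 L/min is thus about 2% (1.4/79.1) to 20% (6.4/31.6) of one standard error.

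A false shift of 10 L/min, larger than any of these, would raise the two-sided 5% error of a pairwise t test with 20 per group to 6.1% at SD 100 and 5.2% at SD 250. At an SD of 50, the initial planning value, it would be 9.5%. Covariate adjustment that shrinks the residual SD would move the answer in that direction.

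**Acquisition for comparison**

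Efforts continue "until five coughs of similar PECF are recorded". The article states neither a tolerance for similarity nor a maximum number of efforts. With a within-person SD of 15 to 30 L/min (assumed), the mean of the best five of 10 efforts exceeds the mean of exactly five efforts by about 11 to 22 L/min; with 8 efforts the excess is about 8 to 17 L/min. Effort counts that differed by arm could therefore matter more than trace reading, and masked derivation would not remove that.

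**The case against.** The strongest reply has four parts.

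- **The reader is not identified.** A journal article may leave this to the full protocol, and the files may already be coded. This stands as a limit on the wording. A reader might infer that the documents show an unblinded person deriving the primary outcome. They show only that this is likely.
- **The selection is by rule.** Taking the five highest peaks leaves little discretion, and the article describes no judgement about leak, drift or artefact. This stands in part: the ranking is a rule, but what qualifies as a cough is not stated. It is also wrong to infer that PECF is never seen live, since stopping at five coughs of like size implies some viewing during the session.
- **The limitation is already disclosed.** That is true of investigator blinding in general. Disclosure does not replace mitigation at a step where it is available.
- **The effect is trivial.** A fall of 5.7 to 17.1 L/min, or 11% to 34% of the 50 L/min design difference, may look serious. That figure is for one affected participant under assumed inputs, not for an arm difference. The arm-level shift is small beside the standard error. This stands, and it keeps the point minor.

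A reader might also conclude that such bias could never be corrected. The documents do not support that: the recordings are digital, so if the files are kept a masked re-derivation remains possible.

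**Conclusion.** The point holds as a cheap improvement, not as an error in the plan. PECF comes from stored traces, one investigator who knows the allocation performs all study procedures, and no masking of the derivation is described. This step can be masked without extra staff.

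The conclusion rests on the inference that this investigator reads the traces, and on the raw files having been kept. The size of any bias cannot be estimated from the article. It is probably small beside the observed SD of 100 to 250 L/min.

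Masked derivation would not make the primary outcome a blinded assessment. Coaching, mask seal and the decision to stop remain with the unblinded investigator and are probably the larger exposure.

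**What to change.** - State who derives PECF from the traces and whether that person can see arm or visit. If coded reading is already in place, one sentence settles the point.
- Store every trace under a random code without arm or visit label, keeping each session's calibration attached.
- Extract PECF for the five highest coughs with one fixed, scripted rule for validity and peak detection. Apply it to all on-site and off-site files in random order, and state how the five values are summarised.
- Lock the values before linking them to allocation.
- Re-derive the traces already collected in the same way.
- Keep unblinded acquisition in the list of limitations.

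The same investigator can run the script, so no new staff, tests or participants are needed, and sample size and power are unchanged. The cost is writing and checking the script (reflex bouts included), converting files from two acquisition platforms, and re-processing time. The documents put no figure on this.

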### Sample size

The initial sample-size calculation was based on observations from a cross-sectional study of acute stroke patients
[44] and a one-way analysis of variance (ANOVA) model of statistical analysis
[60,61]. For group sizes of less than 50, ANOVA assumes that data are normally distributed and that variances are equal. For the purpose of this sample-size calculation, these assumptions were made. With an estimated group standard deviation (SD) of 50 L/min for the main outcome measure (voluntary cough PECF at the primary end point), a sample size of 16 subjects per group gives the study 80% power to detect a 50 L/min difference between groups at the 5% significance level. Assuming an attrition rate of 20%, 20 subjects per study group are required, giving a total sample size of 60.

The sample-size calculation was reviewed after the first 40 participants completed their participation in the study. At this point, participant attrition was higher than anticipated (32%), and primary outcome data showed greater variability than initially assumed, with group SD ranging from approximately 100 to 250. Table 
1 shows estimates of the required number of participants per group to give the study 80% power at the 5% significance level, according to different treatment-effect sizes and different group standard deviations. Taking into account these observed data, the decision was made to increase the study sample to 20 participants per group. This group size was selected to give higher statistical power should the data show large within-group variability. Also, it was considered a realistic recruitment target, given the observed rate of recruitment and the resources available. Taking into account a dropout rate of approximately 30%, the revised target sample is 90 subjects, whereby recruitment will be concluded early once 20 participants per group complete the primary study end point.

**Table 1 T1:** Sample-size calculation

**Expected treatment effect (L/min)**	**Expected SD within group (L/min)**					
	**50**	**100**	**150**	**200**	**250**	**300**
50	15	58	125	250	400	600
100	5	15	35	60	95	125
150	<5	8	15	26	42	58
200	<5	5	10	16	24	34

Estimates of required number of participants per study group to give 80% power at the 5% significance level, according to different expected treatment-effect sizes and different expected group standard deviations (SDs) of the primary outcome (peak expiratory cough flow (PECF) of voluntary cough).

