### Statistical analysis

Descriptive statistics will be used to present group characteristics at baseline; to compare study completers with participants who discontinued the study; and to compare participants with good training completion with those with poor training concordance. Training-safety data will be summarized descriptively and compared against pre-set safety parameters (standard safe ranges of vital parameters as used in clinical practice).

Inferential statistics will be used to evaluate the effect of treatment on the primary and secondary outcome parameters. The hypotheses under investigation are as follows: RMT (inspiratory or expiratory) is effective for improving voluntary cough effectiveness (voluntary cough PECF); RMT (inspiratory or expiratory) is effective for improving reflex cough effectiveness (reflex cough PECF); expiratory muscle training is effective for improving expiratory muscle strength (MEP); inspiratory muscle training is effective for improving inspiratory muscle strength (MIP); RMT (inspiratory or expiratory) is effective for reducing the incidence of pneumonia.

The sample-size calculation followed an ANOVA model of inferential statistical analysis. However, it is anticipated that the study sample will show considerable heterogeneity, in which case, an analysis of covariance (ANCOVA) model is more powerful in detecting a difference in study arms
[62]. ANCOVA will be used to compare group means of voluntary and reflex cough PECF, MEP, and MIP at the primary end point (day 29). The following covariates will be adjusted for: gender, age, smoking, stroke severity (NIHSS score), training intensity, and a predictor variable for “missingness”, which will be determined through logistic regression. Fisher Exact test will be used to compare the incidence of pneumonia from baseline through week 4 between the three study groups. Adjustments for multiple testing will be made by using the Benjamini-Hochberg method
[63].

Four approaches to dealing with missing values will be compared in a sensitivity analysis: intention-to-treat analysis, substituting missing values through predictive model-based imputation
[64]; intention-to-treat analysis, substituting missing values through propensity score imputation
[65]; intention-to-treat analysis, substituting missing values with baseline data; and complete case analysis, using only data from participants who completed the primary end point.

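### Interim group SDs differ up to 2.5-fold, yet nothing in the ANCOVA plan covers unequal variances, so contrasts with sham from a three-arm model may be miscalibrated

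*Protocol article*

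**What the plan says.** The Sample size section of the protocol article starts from a one-way ANOVA and states: "For group sizes of less than 50, ANOVA assumes that data are normally distributed and that variances are equal". The next sentence limits the scope: "For the purpose of this sample-size calculation, these assumptions were made". The initial calculation uses one SD for every group ("With an estimated group standard deviation (SD) of 50 L/min") and concludes that "16 subjects per group gives the study 80% power to detect a 50 L/min difference between groups at the 5% significance level".

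The calculation was reviewed after 40 participants had finished. Attrition was then 32%, and "primary outcome data showed greater variability than initially assumed, with group SD ranging from approximately 100 to 250". The target became 20 completers per group, with up to 90 recruited. Table 1 again uses one common SD in each cell.

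The Statistical analysis section says: "ANCOVA will be used to compare group means of voluntary and reflex cough PECF, MEP, and MIP at the primary end point (day 29". It gives sample heterogeneity and power as the reason for moving from ANOVA to ANCOVA. It names the covariates, the Benjamini-Hochberg adjustment and four sensitivity analyses, all of which concern missing data. It mentions no unequal-variance model, robust standard error, transformation or variance check.

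**The concern.** The article names an assumption that matters at its own group size, reports data that point against it, and then fixes an analysis that in its usual form makes the same assumption. An SD range of 100 to 250 is a variance ratio of (250/100)² = 6.25.

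A pooled residual variance averages over the arms. A contrast that leans on the most variable arm then gets a standard error that is too small, and a contrast between less variable arms gets one that is too large. The hypotheses concern inspiratory or expiratory training (for cough flow), expiratory training (for MEP) and inspiratory training (for MIP), so they call for comparisons with sham that the overall F test does not provide. The Benjamini-Hochberg step takes those p-values as valid. The intervals also matter, because the stated aim is to estimate the size of effect for a larger trial.

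**Working it through.** **The plan's own figure.** With SD 50, difference 50, 80% power and two-sided 5% (sidedness is assumed), n = 2(1.96 + 0.84)² × 50²/50² = 15.7, so 16 per group. A three-arm ANOVA with means 0, 0, 50 also gives 16 (power 0.81). Allowing for 20% attrition, 16/0.8 = 20. The stated figures reproduce under equal variances.

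**Basis of the interim SDs.** 40 × (1 − 0.32) ≈ 27 with endpoint data, or about 9 per arm. If the true variances were equal and the data normal, three arms of 9 would show an SD ratio of 2.5 or more about 4% of the time.

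**Effect of pooling, 20 per arm.** For a contrast with weights c, the ratio of the true to the pooled standard error is

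r = √[Σc²σ² / (Σc² × mean of σ²)].

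The true error rate is then roughly P(|t| > 2.00/r) on 57 df.

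- *Sham 250, both active arms 100.* Mean variance = (62,500 + 10,000 + 10,000)/3 = 27,500. For the average of the active arms versus sham, Σc²σ² = 62,500 + 2,500 + 2,500 = 67,500 and Σc² = 1.5, so r = √(67,500/41,250) = 1.28. The pooled interval is 1/1.28 = 0.78 of its proper width.
- *Sham 100, active arms 175 and 250.* Mean variance = (10,000 + 30,625 + 62,500)/3 = 34,375. Σc²σ² = 10,000 + 0.25 × 93,125 = 33,281, so r = √(33,281/51,563) = 0.80. The pooled interval is about 1.24 times its proper width.

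**Simulated type I error** (nominal 5%, normal data, no covariates, 100,000 null trials per pattern; the middle SD and the order of the arms are not in the article and are varied here):

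| SDs (20 per arm) | Overall F | Contrasts from the pooled three-arm model |
|---|---|---|
| Sham 250, active 100 and 100 | 6.9% | Each active v sham 9.0%; combined active v sham 12.7%; active v active 0.2% |
| Sham 250, active 100 and 175 | 5.9% | Combined active v sham 9.9% |
| Sham 100, active 175 and 250 | 5.9% | 175 arm v sham 1.3%; 250 arm v sham 5.8%; combined 1.7% |
| 100, 125, 150 (milder) | 5.3% | Pairwise 2.9% to 7.4% |
| All equal | 4.9% | 4.8% to 5.0% |

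One layout goes lower still: if sham and one active arm both have SD 100 and the other active arm 250, the contrast between the two low-SD arms has an error rate of 0.2%.

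With five covariates in the model (8,000 runs), the overall F ran at 5.5% to 6.1% and pairwise contrasts at 0.4% to 9.2%.

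**Remedies.** Arm-specific variances with Satterthwaite df gave 4.8% to 5.1% in every pattern (no covariates). ANCOVA with HC3 standard errors and five covariates gave 2.4% to 4.4% pairwise, which is conservative.

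**Unequal completers.** With SDs 100/175/250 and 28/23/20 completers (largest SD in the smallest arm), the overall F was 7.9% and the worst contrast 11.2%. With the order of numbers reversed, they were 4.2% and 7.6%.

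**The case against.** The strongest reply is that the plan does not contradict itself. The equal-variance sentence is about ANOVA and is confined to sizing. The article never writes that the ANCOVA has a common variance, and a condensed article may leave residual-variance options to a fuller plan. This stands in part: pooling is the ordinary meaning of ANCOVA, not the document's wording. But the article does fix the model, covariates, multiplicity method and sensitivity analyses, and it says that the analysis plan was revised as the data became clearer. Variance handling belonged in that list once the SDs had been seen.

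A reader might infer that ANCOVA was adopted to deal with the unequal SDs. The text does not say so: its stated reason is heterogeneity of the sample and power, and its response to the SDs was Table 1 and a larger target.

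A reader might also infer that the primary test is badly invalid. With equal arms the overall F is close to nominal. No contrast set is defined, and if each comparison used its own two arms only, with equal numbers, the error would be about 5.0% to 5.4%. The 13% figure needs sham to be the most variable arm and both active arms to sit at 100. Completers of 16/22/22 with sham SD 250 would give 17% for combined active versus sham. But 16 in an arm can arise only if the cap of 90 is reached before every arm has 20, and three of the four missing-data approaches impute and so keep arms near equal.

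The evidence for unequal variances is also limited: raw, approximate SDs from about 9 per arm, for the primary outcome only. Heavier-tailed data (t with 5 df, an assumption) would produce a ratio of 2.5 or more about 14% of the time under equal variances.

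**Conclusion.** The point holds in a limited form. The article's own data cast doubt on an assumption that it recognises as relevant at this group size, and the planned analysis leaves the matter open. The consequence is conditional on two things: that the SD differences persist after covariate adjustment, and that contrasts are taken from the three-arm model. On those conditions, comparisons with sham run from about 1% (0.2% in one extreme layout) to 13% at a nominal 5%, in a direction that depends on which arm is more variable. They run at about 3% to 7% for the milder SDs. Intervals are off to match. The overall F is only slightly inflated with equal arms. The documents do not support saying that the error rates are known to be wrong, or that any one of these figures is the trial's actual rate. The pilot status softens the impact but does not remove it, since inferential tests with multiplicity adjustment are planned.

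**What to change.** For voluntary and reflex PECF, MEP and MIP, fit the ANCOVA with arm-specific residual variances and Satterthwaite (or Kenward-Roger) degrees of freedom for the contrasts with sham. State those contrasts explicitly. Report the equal-variance version as a sensitivity analysis. This is one option in the model code and needs no further data. The downside is slightly wider intervals if the variances prove equal. HC3 standard errors should not be the preferred route, because they were conservative with covariates at this sample size.
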